## 2. Materials and Methods

### 2.1. Design, Study Population, Recruiting Centers and Trial Registration

This is a multi-center prospective observational study. A sample of outpatients with SCD and MCI due to AD will be enrolled from three sites in Lombardy (Italian Region): “San Gerardo” Hospital (Monza), “Luigi Sacco” University Hospital (Milan), and Fondazione IRCSS Ca’ Granda Ospedale Maggiore Policlinico (Milan, Italy).

Individuals with SCD will be detected according to Jessen and colleagues’ criteria [79] while prodromal AD will be defined according to Dubois and colleagues’ criteria [80], respectively. Healthy older adults will be enrolled through advertisements distributed in social centers for senior citizens in Milan (Italy) and through popular science events (conferences, webinars) concerning research in AD prevention. The three sites currently use the neuropsychological batteries reported in the Appendix A. Healthy older adults will be assessed by the experimenters at the Department of Psychology, Catholic University (Milan, Italy), by adopting the same neuropsychological battery as the IRCSS Ca’ Granda Ospedale Maggiore Policlinico (Milan, Italy). Family medical history of AD was collected during clinical interview along with laboratory tests results and neuroimaging findings for outpatients with SCD and MCI due toAD.

For the whole sample, inclusion criteria will involve the following: age from 65 to 85 years; education not less than 5 years; basic ICT skills. All participants will be excluded from the study according to the presence of visual, hearing, or motor impairment significantly interfering with SN tasks; neurological/psychiatric disease or other medical conditions preventing SN; history of alcohol or drugs addiction; intake of psychotropic drugs; and presence of dementia. Recruitment will end on 29 February 2024.

With the aim of obtaining results that can be generalized, sociodemographic and clinical features of the sample to be recruited will be analyzed among the research team members prior to the sample enrollment according to epidemiological studies carried out on the Italian elderly population, specifically including MCI patients [81,82,83] and individuals with SCD [84].

The Uniform Resource Locator for the clinical trial registration is the following one: https://classic.clinicaltrials.gov/ct2/show/NCT05944601 (identifier: NCT05944601) (accessed on 13 July 2023).

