Before the navigation of the urban garden, all participants will equip the Howdy Senior^©^ (Comftech S.r.l., Monza, Italy) device (Figure 6), a wearable monitoring system. All participants will be recorded according to cardiac and respiratory parameters *at rest* for five minutes and during the naturalistic experiment (Table 1). These data will be available thanks to the instant reports produced by the connected “Howdy Senior App” set up on the experimenter’s smartphone.

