**Figure 6 jpm-14-00192-f006:**
[figure not shown]
Howdy Senior system components. The electronic unit (white) detects heart rate, respiratory rate, and body position. It is equipped with five automatic snaps on the back and communicates with the Howdy app via Bluetooth. The electronic unit can be combined with different textile units: male/female top with sensors and belt. The electronic unit and textile unit are connected using the automatic snaps. The Howdy Apps works on smartphones and tablets running Android 8.0 or later.

**Table 1 jpm-14-00192-t001:** Cardiac, respiratory, and accelerometer parameters collected by the Howdy Senior App.

**Cardiac system functions** *Time domain over RR intervals parameters*	avgRR: mean of R2R interval; SDRR: standard deviation of R2R interval; avgHR: mean of Heart rate; SDHR: standard deviation of Heart rate; MSSD: mean of square successive differences between normal heartbeat; RMSSD: root mean square of square of successive differences between normal heartbeat; lnRMSSD: natural log of RMSSD; hrvScore: normalized lnRMSSD value using as scaling factor the value 6.5; RR50: number of successive absolute difference greater than 50 ms; pRR50: percentage of number of successive absolute difference greater than 50 ms over the number of elements in the analyzed window; SD1: standard deviation along the minor axes of the Poincare plot; SD2: standard deviation along the major axes of the Poincarè plot; Stress index.
**Cardiac system functions** *Frequencies domain over RR intervals parameters*	LF: power in the low frequency band affected by sympathetic nervous system (SNS); HF: power in the high frequency band affected by parasympathetic nervous system (PNS); LF/HF: ratio between the power in low and high frequency band.
**Respiratory system functions**	avgBR: mean of BR; SDBR: standard deviation of BR.
**Accelerometer parameters**	AccXavg, AccYavg, AccZavg: mean of accelerations for X, Y, Z axes; AccXsd, AccYsd AccZsd: standard deviation of accelerations for X, Y, Z axes; AccXrms, AccYrms, AccZrms: root mean square of accelerations for X, Y, Z axes.

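### Participants with a rhythm disorder or pacemaker enter the heart-rate-variability correlations unrestricted, which may attenuate or distort the cardiac part of the secondary physiology analysis

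*Protocol article*

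**What the plan says.** Section 2.1 sets the entry criteria: "age from 65 to 85 years; education not less than 5 years; basic ICT skills". Besides sensory or motor impairment that interferes with the tasks, and addiction, the medical exclusion is "neurological/psychiatric disease or other medical conditions preventing SN" and the remaining ones are "intake of psychotropic drugs; and presence of dementia". Heart rhythm, implanted devices and rate-limiting drugs are not mentioned.

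Section 2.3.2 applies the wearable to everyone: "All participants will be recorded according to cardiac and respiratory parameters", for five minutes at rest and then during the naturalistic test.

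Table 1 lists 16 cardiac outputs. Thirteen are RR-variability measures: SDRR, MSSD, RMSSD, lnRMSSD, hrvScore, RR50, pRR50, SD1, SD2, the stress index, LF, HF and LF/HF. The table links LF and HF to sympathetic and parasympathetic activity. MSSD and RMSSD are defined on normal heartbeats ("RMSSD: root mean square of square of successive differences between normal heartbeat"); SDRR, RR50, pRR50, SD1, SD2, LF and HF carry no such qualifier. The respiratory outputs are "avgBR: mean of BR; SDBR: standard deviation of BR".

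Section 2.4 correlates step variability, as a marker of moments of hesitation, with mean cardiac and respiratory values, by Pearson or, if assumptions fail, by Spearman. It states no restriction by rhythm, device or medication. Section 3 expects the association with hesitation particularly in respiratory function.

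**The concern.** The RR-based indices are read as signs of autonomic response to disorientation. In atrial fibrillation or with frequent ectopy, beat-to-beat variability is governed by the arrhythmia. With pacing it is governed by the device. For these people the autonomic reading does not hold, yet nothing in the criteria or the analysis text separates them, and the age range makes such people plausible recruits.

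At stake is the cardiac half of the physiology correlation. A few values that are extreme or unrelated to gait can weaken a real association or, by chance alignment with gait, create or exaggerate one. The article presents physiological correlates of disorientation as something not yet shown in the literature (Section 1.5), so a weak or unstable cardiac result would be hard to interpret.

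**Working it through.** **The plan's own figures.** The article gives no assumed size for this correlation and no frequency of arrhythmia or pacing, so there is nothing to reproduce for this analysis. The sample size of 76 was set for a different model, a multiple regression with f² = 0.15, 3 predictors, α = 0.05 and power 0.9. Those inputs give 99 rather than 76 (power at 76 is about 0.80). That is a separate matter; here 76 is taken as planned.

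**Step 1. Who enters.** Eligibility (Section 2.1) has no rhythm or device criterion. All participants are recorded (Section 2.3.2). No subset is named for the correlation (Section 2.4). A participant with atrial fibrillation who can walk Route A (80.5 m) is therefore analysed with everyone else.

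**Step 2. Assumptions for an illustration.** n = 76 is from the article. The following are assumed: true correlation ρ = -0.40 in unaffected participants; m = 4 or 8 affected participants (π = m/76 = 5.3% or 10.5%); their cardiac index distributed N(3, 1) on the scale where unaffected values are N(0, 1), and unrelated to gait; two-sided 5% test.

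**Step 3. Pearson, closed form.** The mixture has covariance (1 - π)ρ and index variance 1 + 9π(1 - π), so

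r = (1 - π)ρ / √[1 + 9π(1 - π)], and power ≈ Φ(|atanh r|·√(n - 3) - 1.96).

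- m = 0: r = -0.40; 0.4236 × √73 = 3.62; power 0.95.
- m = 4: r = -0.3789 / √1.4488 = -0.315; 0.3259 × √73 = 2.785; power 0.80.
- m = 8: r = -0.3579 / √1.8476 = -0.263; 0.2696 × √73 = 2.304; power 0.63.

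Simulation gives the same values within simulation error.

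**Step 4. Spearman and exclusion, by simulation.**

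| Affected | Pearson, all 76 | Spearman, all 76 | Pearson, affected left out |
|---|---|---|---|
| 0 | 0.95 | 0.93 | – |
| 4 | 0.80 | 0.87 | 0.94 (n = 72) |
| 8 | 0.63 | 0.77 | 0.93 (n = 68) |

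If a Shapiro test on the cardiac index decides between the two coefficients, power is 0.86 or 0.75 with 4 or 8 affected.

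**Step 5. Range under milder assumptions.** Suppose instead that the affected values have the same mean as the rest, are unrelated to gait, and have k times the variance. Then r = (1 - π)ρ / √[(1 - π) + πk]. For ρ = 0.40 (sign ignored) and Pearson:

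| π | k = 1, all 76 | k = 4, all 76 | Affected left out |
|---|---|---|---|
| 5% | 0.93 | 0.89 | 0.94 (n = 72) |
| 10% | 0.90 | 0.80 | 0.93 (n = 68) |
| 20% | 0.81 | 0.60 | 0.90 (n = 61) |

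The loss runs from almost nothing to substantial, depending on frequency and extremeness. In every scenario, leaving the affected participants out costs less than keeping them.

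**The case against.** The case against giving this much weight is good, and most of it stands.

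- *The planned fallback helps.* Section 2.4 checks distributions first and names Spearman for this correlation. That roughly halves the illustrated loss, though it does not remove it.
- *Rate-limiting drugs are different.* A reader might infer that beta-blocked participants also yield invalid RR values. They do not: the intervals are genuine measurements with an altered or blunted response. That is confounding or heterogeneity.
- *The affected result is narrow.* The physiology correlation is secondary, did not drive the sample size, and is expected to show mainly in respiration, which does not rest on RR intervals.
- *No group comparison of cardiac indices is stated.* A reader might infer that an imbalance in arrhythmia could pass for a disease-related stress signature. The planned three-group ANOVA covers gait parameters and the navigation-complaints questionnaire, so such an effect could arise only indirectly, through the pooled correlation.
- *Some beat selection is implied.* MSSD and RMSSD refer to normal heartbeats, and lnRMSSD and hrvScore derive from RMSSD. The other RR indices have no such wording.
- *Artefact and recording-quality rules may sit in a fuller document.* This is fair, and their absence from an article is no fault. But a beat-level artefact rule would not fully replace identifying people in persistent arrhythmia or with a pacemaker, which needs medical history.

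**Conclusion.** The point holds in limited form. As written, participants whose RR variability is driven by arrhythmia or pacing would be analysed as if it were autonomic, and the cardiac part of the step-variability correlation may be attenuated or distorted as a result. The effect cannot be sized from the article. The illustrated drop to about 0.80 or 0.63 (Pearson), or 0.87 or 0.77 (Spearman), rests on an assumed correlation of -0.40, 4 or 8 affected participants, and a 3 SD shift.

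The article does not support saying that dilution is certain, that the whole physiology result is compromised, or that the navigation endpoints are touched. This is a cheap improvement of minor priority.

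**What to change.** Leave eligibility for the study and the navigation tasks unchanged.

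1. From medical history, record known arrhythmia (including atrial fibrillation and frequent ectopy), a pacemaker, and rate-limiting or antiarrhythmic drugs. Do the same retrospectively for those already enrolled.
2. Define a cardiac analysis set that leaves participants with arrhythmia or a pacemaker out of the RR-based analyses only. They stay in the respiratory, gait and navigation analyses.
3. Repeat the RR-based correlations without participants on rate-limiting drugs, as a sensitivity analysis, because their values are confounded, not invalid.
4. Report how many participants fall in each category, by group.

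The cost is three history items, one analysis-set definition and one extra run. The downside is a slightly smaller n for the cardiac correlations: in the illustration, 72 or 68 instead of 76, with power at 0.94 or 0.93 against 0.95 if all 76 recordings were usable.

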### 2.4. Statistical Analysis

Data distribution will be first checked on collected variables by assessing skewness and kurtosis values, by performing normality and heteroscedasticity tests, and by visually inspecting histogram and Q–Q plots. Based on data meeting or non-linear model assumption, either parametrical or non-parametrical analyses will be performed. By means of the R marco *pwr* [86], the minimal sample size has been set as 76 participant, based on a power analysis for a multiple regression model that took into account the following parameters: α = 0.05; 1-β = 0.9; *f*^2^ = 0.15 (medium effect size, in order to be conservative) [87]; and numbers of predictors: 3 (age, APOE genotypes, and belonging to each group, with the last two predictors as dummy variables).

We will detect the route disorientation scores, i.e., WTs and MsH, as already described in Puthysserypaddy et al. [64]. Accordingly, all the violations in terms of deviations from the pre-established return path (i.e., movement at an intersection onto a different path as compared to the original one, or non-roadable walkways) will be written down by the experimenter as WTs in a pre-set paper grid for *Route A*. The overlaps with the *Route A* return path, and, likewise, non-roadable walkways will be written down by the experimenter as WTs in a pre-set paper grid for Route *B*. Further, we will detect the MsH as the participant either slows down/stops and looks around to aid orientation or verbally admits to the experimenter that he/she is unsure about his/her whereabouts, both for *Route A* and the *Route B* return path.

In addition to the experimenter visually identifying and recording the frequency of the MsH with a stopwatch and a pre-set paper grid, we will measure this variable more objectively using the Howdy Senior integrated accelerometer. For this purpose, we will use the motion sensor of the sensorial body measuring the individual’s linear acceleration in the three axes (i.e., x, y, z). To segment the magnitude signals, according to Schaat et al. [88], we will adopt time intervals of 10 s, with an overlap of 5 s between subsequent intervals because a 10 s segment is sufficiently long to capture multiple steps during walking, thus revealing important behavioral changes. In this way, we will detect the MsH as a signal flattened along the three axes. Further, given that physiological parameters may alter depending on the MsH, we will also investigate the relationship between step variability and co-occurring time-dependent cardiac and respiratory parameters detected by the Howdy App, expressed as mean values, via Pearson’s correlation coefficients or their non-parametric equivalent (i.e., Spearman’s rank order correlation). Moreover, we will run a one-way ANOVA (or its non-parametric equivalent) to compare performances of the three subgroups on gait parameters collected through the Aptive app and the SSNC questionnaire. In order to explore potential association between specific neurocognitive functions and SN impaired abilities, Pearson correlations or their non-parametric equivalent (i.e., Spearman’s rank order correlation) will be further performed between the AppleGame/DNT-mv results and the neuropsychological tests used in the sending centers, especially visual–constructive skills and executive functions (see Appendix A). Given the difference of the neuropsychological battery used in the sending centers, we will group tests according to the primary cognitive domain involved and we will divide the scores obtained in a dichotomous way for each participant according to the reported cut-off values in the test manuals, i.e., 0 = pathological performance; 1 = normal performance.

Finally, a linear/generalized linear regression analysis will be run, taking into account the drop errors of the AppleGame subtasks—considered one at a time—as independent variables, and the total number of “wrong turns” (WTs)/total number of “moments of hesitation” (MsH) (in seconds) of the DNT-mv as dependent variables.

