## Abstract

Spatial navigation (SN) has been reported to be one of the first cognitive domains to be affected in Alzheimer’s disease (AD), which occurs as a result of progressive neuropathology involving specific brain areas. Moreover, the epsilon 4 isoform of apolipoprotein-E (APOE-ε4) has been associated with both sporadic and familial late-onset AD, and patients with mild cognitive impairment (MCI) due to AD are more likely to progressively deteriorate. Spatial navigation performance will be examined on a sample of 76 community-dwelling senior citizens (25 healthy controls; 25 individuals with subjective cognitive decline (SCD); and 26 patients with MCI due to AD) via a virtual computer-based task (i.e., the AppleGame) and a naturalistic task (i.e., the Detour Navigation Test—modified version) for which a wearable device with sensors will be used for recording gait data and revealing physiological parameters that may be associated with spatial disorientation. We expect that patients with MCI due to AD and APOE-ε4 carriers will show altered SN performances compared to individuals with SCD and healthy controls in the experimental tasks, and that VR testing may predict ecological performance. Impaired SN performances in people at increased risk of developing AD may inform future cognitive rehabilitation protocols for counteracting spatial disorientation that may occur during elders’ traveling to unfamiliar locations. The research protocol has been approved by the Ethics Committee of the Istituto Auxologico Italiano. Findings will be published in peer-reviewed medical journals and discussed in national and international congresses.

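### Choosing the test from the raw distribution of the variables may leave the first-endpoint group comparisons without age and APOE; one adjusted model per outcome, checked on its residuals, is safer

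*Protocol article*

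**What the plan says.** All of this is in Section 2.4 of the protocol article unless another place is named.

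- **The check.** "Data distribution will be first checked on collected variables by assessing skewness and kurtosis values", followed by normality and heteroscedasticity tests, histograms and Q–Q plots. Residuals are not mentioned, and no cut-off or order of precedence among these diagnostics is given.
- **The decision.** "Based on data meeting or non-linear model assumption, either parametrical or non-parametrical analyses will be performed".
- **The sizing model.** A multiple regression with "numbers of predictors: 3 (age, APOE genotypes, and belonging to each group, with the last two predictors as dummy variables". This is the only place where age, APOE and group appear together.
- **Named non-parametric options.** There are two. One is for gait parameters and the navigation-complaints questionnaire: "we will run a one-way ANOVA (or its non-parametric equivalent". The other is Spearman in place of Pearson correlation. Neither carries covariates.
- **Second endpoint.** Wrong turns and moments of hesitation are regressed on drop error by a linear or generalized linear model.
- **First endpoint.** Section 1.7 asks for group differences on the virtual and naturalistic tasks. Section 3 expects higher drop errors, wrong turns and hesitation in MCI, and a pure path integration deficit in ε4 carriers irrespective of group. No non-parametric alternative is named for these comparisons.

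**The concern.** A linear model assumes something about the errors around its fitted values. The marginal distribution of an outcome mixes those errors with the effects of group, age and genotype, so inspecting the variable does not test the assumption that matters.

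The first-endpoint outcomes are a distance, a count, and a count or duration. Their natural skew makes the non-parametric branch likely. If that branch is the rank analogue of a one-way ANOVA, the only rank group comparison mentioned, two things are lost:

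- The APOE hypothesis needs APOE and group in the same model, and a rank comparison of three groups has no place for APOE.
- Age adjustment disappears. Ages run from 65 to 85 (Section 2.1). Controls come from advertisements and public events, patients from three hospitals, and no matching is stated, so an age difference is plausible.

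The same question could then be answered by an adjusted or an unadjusted test, depending on diagnostics read after the data are in.

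**Working it through.** **1. The plan's own figure.** Inputs: "α = 0.05; 1-β = 0.9"; f² = "0.15 (medium effect size, in order to be conservative"); 3 predictors; "the minimal sample size has been set as 76 participant". For the overall F test with u numerator and v denominator degrees of freedom, λ = f²(u + v + 1) and N = v + u + 1, with v rounded up. With u = 3 and power 0.90, v = 94.48, so N = 95 + 3 + 1 = 99, not 76. At N = 76 the power is 0.796. The figure of 76 is not reproduced. That is a separate matter, and the sizing calculation is used here only to show that the intended model contains age, APOE and group.

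**2. Does a check on the raw variable mislead?** Take normal residuals of equal spread and shift only the MCI group. A Shapiro–Wilk test on the raw outcome rejects in 5%, 6%, 14% and 71% of samples for shifts of 1, 1.5, 2 and 3 SD. On residuals it rejects in about 5%. With equal spread, group separation alone misdirects the check only when it is large. Skewness is the commoner route.

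**3. Which branch would skewed outcomes take?** With gamma errors (shape 1.5, assumed) the raw-variable test rejects normality in 95–100% of samples, so the rank branch is taken almost always.

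**4. What happens to false group differences?** Group sizes are those of the Abstract ("25 healthy controls; 25 individuals with subjective cognitive decline (SCD); and 26 patients with MCI due to AD"). There is no true group effect, and each scenario has 2,000 runs (Monte Carlo standard error about 0.5 points at 5%). The two-stage rule is modelled as Shapiro–Wilk on the raw outcome, then Kruskal–Wallis if rejected, otherwise ANCOVA with age, APOE and group. The article gives no age or ε4 distribution by group, so every scenario is an assumption. Age gap means controls to MCI, in SD of age. The age slope is 0.3 SD of outcome per SD of age in every row shown.

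| Age gap | ε4 carriage (control/SCD/MCI) | APOE effect (SD) | Two-stage | One-way ANOVA, no covariates | ANCOVA | Rank ANCOVA |
|---|---|---|---|---|---|---|
| 0 | 20/20/20% | 0.4 | 4.7% | 4.9% | 5.1% | 5.3% |
| 0.4 | 20/20/20% | 0 | 7.4% | 6.6% | 5.4% | 5.6% |
| 0.8 | 20/20/20% | 0 | 12.8% | 9.6% | 4.1% | 5.0% |
| 0.4 | 20/30/50% | 0.4 | 12.8% | 11.0% | 4.4% | 4.8% |
| 0.8 | 20/30/50% | 0.4 | 19.8% | 16.0% | 4.8% | 4.4% |

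Over all skewed scenarios the two-stage rule gives:

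- 4.1–5.6% when the groups are balanced or the covariates have no effect;
- 6.5–7.4% under mild confounding, which is a small excess given the Monte Carlo error;
- 11–13% under moderate confounding;
- 19.8% in the strongest case.

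Over all scenarios, including normal errors, ANCOVA stays at 4.1–6.2% and rank ANCOVA at 4.2–6.4%. With normal errors the two-stage rule stays at 4.2–6.5%.

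**5. Cause.** Unadjusted ANOVA is inflated as well (9.6% and 16.0% in the two rows with the 0.8 SD gap), while rank ANCOVA, which ranks but keeps the covariates, is not. The excess comes from leaving out age and APOE.

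**The case against.** The strongest reply is that the damaging step is not written down. Nothing in Section 2.4 says that the age, APOE and group regression gives way to a Kruskal–Wallis test. That much stands, and more stands with it:

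- For gait and the questionnaire, the parametric one-way ANOVA has no covariates either, so switching to ranks drops nothing.
- For the second endpoint, generalized linear regression already provides for counts and skewed outcomes.
- Pooling across groups is not stated, and a single automatic normality test is not what the text describes. It lists several numerical and graphical checks and refers, in garbled wording, to model assumptions. A team could reasonably apply these to residuals.
- A fallback test is commonly named in the analysis plan, which is not shown.
- The inflation depends on imbalance that the article neither reports nor predicts.

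A reader might infer that the plan discards age and APOE for skewed outcomes and so inflates false group differences. The article does not support that as a statement of fact.

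The objection does not remove the rule itself. The text directs the check at the variables, lets it choose the class of analysis, and is the only guidance for the first-endpoint outcomes. The point rests on that stated rule, not on a missing detail.

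**Conclusion.** The concern holds in a limited form: the rule checks the wrong quantity and leaves open an unadjusted rank analysis of drop error, wrong turns and hesitation at the first endpoint. If that route is taken, the APOE hypothesis cannot be tested as posed, whether or not the groups are balanced. False group differences become more frequent only if the groups differ in age or ε4 carriage and those factors affect performance: about 6.5% to 20% in the assumed scenarios, against about 5% for an adjusted model, with no inflation under balance. These rates rest on the assumed gamma errors, slopes, gaps and carriage rates, and on reading the rule as one normality test followed by Kruskal–Wallis. They show direction and plausible size and do not predict this study's error rate. The change is worth making before analysis, but the point does not invalidate the design.

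**What to change.** For each first-endpoint outcome, replace the distribution-based choice with one pre-specified model containing group, age and ε4 status:

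- **Drop error:** a linear model with robust standard errors, or on the log scale.
- **Wrong turns:** a count model such as negative binomial regression.
- **Hesitation:** a generalized linear model or rank ANCOVA that allows zeros, since a participant may never hesitate and a plain log would then be undefined. Section 2.4 describes this outcome both as a frequency and in seconds, so the text should say which is modelled.

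Check the residuals of these models, and state in advance which adjusted alternative applies if they fit poorly. Keep unadjusted rank tests as sensitivity analyses. The existing Pearson or Spearman provision for the correlations can stay.

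The cost is a few lines of text and slightly more analysis work. No further data are needed, because age is known at enrolment and Section 2.2 already has every participant genotyped.

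### The stated sample-size inputs require 99 participants for 90% power, not 76; with 76 the power of the stated calculation is about 80%

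*Protocol article*

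**What the plan says.** Section 2.4 (Statistical Analysis) of the protocol article reports that "the minimal sample size has been set as 76 participant, based on a power analysis for a multiple regression model". The error rates are given as "α = 0.05; 1-β = 0.9". The effect size f² is "0.15 (medium effect size, in order to be conservative", and the model has "numbers of predictors: 3 (age, APOE genotypes, and belonging to each group, with the last two predictors as dummy variables". The software is the R package pwr. The Abstract plans "a sample of 76 community-dwelling senior citizens", split into 25 controls, 25 with subjective cognitive decline and 26 with MCI due to AD (25 + 25 + 26 = 76). The calculated minimum is therefore also the recruitment target. Section 2.4 states no further adjustment that would link these inputs to 76.

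**The concern.** The article gives every input of a standard power calculation and its output, so the output can be checked, and it does not follow from the inputs. If the true power is lower than stated, a null result on the group or APOE hypotheses in the Discussion would be read against a 10% false-negative risk when the actual risk is larger. There is also no margin. The minimum equals the target, so every unusable record lowers power further, and the article's own limitations paragraph warns that the technology may fail.

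**Working it through.** **Inputs** (section 2.4): α = 0.05; target power 0.90; f² = 0.15; numerator degrees of freedom u = 3, from the stated number of predictors; N = 76.

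**Method.** This is the calculation in the regression function of pwr. With denominator degrees of freedom v, the total is N = u + v + 1 and the noncentrality is λ = f²(u + v + 1). Power is P[F′(u, v, λ) > F(1−α; u, v)].

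**Attempt to reproduce the stated figure**

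- For power 0.90 the solution is v = 94.48. Then N = 3 + 94.48 + 1 = 98.48, rounded up to **99**. Check: power is 0.898 at N = 98 and 0.902 at N = 99.
- The article's figure of 76 is not reproduced. The gap is 99 − 76 = 23 participants, which is not rounding.

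**Power at the planned size.** With N = 76, v = 76 − 3 − 1 = 72 and λ = 0.15 × 76 = 11.4. The critical value is F(0.95; 3, 72) = 2.73, and power = **0.796**. The false-negative risk is 1 − 0.796 = 0.204, against 0.10 stated.

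**Effect detectable with 90% power at N = 76.** Solving for f² with u = 3 and v = 72 gives f² = **0.197**.

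**What does give about 76.** At power 0.80 the same inputs give v = 72.71, so N = 76.71, rounded up to 77. It becomes 76 if v is rounded up to 73 and only the 3 predictors are added, without the intercept. This is a plausible origin, but the article does not show it.

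**Other readings of the tested degrees of freedom** (α = 0.05, f² = 0.15). The ranges cover two conventions: λ = f²(u + v + 1), or λ = f²N with v = N − k − 1 for a model with k coefficients besides the intercept.

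| Test | N for 90% power | Power at N = 76 |
|---|---|---|
| Overall, 3 predictors as stated | 99 | 0.796 |
| Overall, 4 coefficients (age, one APOE dummy, two group dummies) | 108 | 0.747 |
| Three-group effect, 2 df | 88 (λ = f²N) | 0.84–0.85 |
| Single coefficient, 1 df | 73 (λ = f²N) | 0.90–0.92 |

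Three groups coded as dummies need two indicators, so counting coefficients strictly makes the overall shortfall larger.

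**Sensitivity to lost records.** The article gives no loss rate. If 10% is assumed for illustration, 68 records are usable (76 × 0.9 = 68.4), v = 64, λ = 0.15 × 68 = 10.2, and power for the 3-df test is 0.74.

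**Size of the assumed effect.** For a three-group factor with equal groups, f = √0.15 = 0.387. If the three means are evenly spaced, the extreme groups differ by f√6 = 0.387 × 2.449 = 0.95 SD. If one group differs from two equal groups, the gap is 3f/√2 = 0.387 × 2.121 = 0.82 SD.

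**The case against.** The strongest reply is that the article gives a number of predictors, not the degrees of freedom tested, and that a single-coefficient test may have been meant. With u = 1 and power 0.90, v = 70.03, rounded up to 71. Adding an intercept and four coefficients gives 71 + 5 = 76, which matches both the stated size and the stated power. Some named hypotheses are of this kind: APOE carriers against non-carriers, and the regressions that enter the AppleGame drop errors singly. The study is also observational, and its first endpoint is exploratory.

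Part of this stands. For a 1-df test the power at 76 is indeed 0.90 to 0.92, so the shortfall does not apply to every comparison in the study. It does not rescue the sentence. The article never mentions a single-coefficient test, and a reader who enters the stated inputs gets 99. With the stated 3 predictors this route gives 71 + 4 = 75, and it reaches 76 only with four coefficients, which is not the number stated. The three-group contrast in the first endpoint still falls short, at 0.84 to 0.85. Even if a 1-df test was intended, the sentence needs correcting, because the tested degrees of freedom are not given.

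**Conclusion.** The concern holds. For the calculation as stated (overall test of 3 predictors, α = 0.05, f² = 0.15), 90% power requires 99 participants. The planned 76 give 79.6%, about 10 percentage points below the claim, and double the stated false-negative risk. This rests on taking the stated number of predictors as the numerator degrees of freedom, the only such figure the article supplies. On other readings the power at 76 runs from 0.75 (overall test with four coefficients) to 0.92 (one coefficient), and the three-group effect lies at 0.84 to 0.85. How the error arose cannot be told from the document, and the conclusion does not depend on it. It should be corrected, since the power claim is wrong as written.

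**What to change.** Keep N = 76 and replace the power statement in section 2.4 with one that matches it, for example: *With 76 participants the overall regression test (α = 0.05, f² = 0.15, 3 tested degrees of freedom) has about 80% power; 90% power is reached for f² of about 0.20.* These figures are true at N = 76 whichever test was intended. If a single coefficient was the intended target, name it, state that its test has 1 degree of freedom, and report the power for the 2-df group effect (0.84 to 0.85) alongside.

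The remark that the effect size was chosen to be conservative is best deleted as well. For a three-group effect, f² = 0.15 means differences of roughly 0.8 to 0.95 SD between groups. This is a minor wording point, separate from the arithmetic.

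The cost is one corrected sentence and a less favourable power figure. No extra participants are needed.
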